### Study setting

We will invite practices from the geographical areas covered by the UK North East and North Cumbria, Yorkshire and Humber, North West Coast, and Greater Manchester National Institute for Health and Care Research (NIHR) Research Delivery Networks (RDNs) to take part in the trial. Practices will not be eligible to participate if they are currently offering health checks to autistic people or who have plans to do so in the near future.

### Recruitment and eligibility criteria

We will recruit two hundred autistic adults via participating practices: approximately 100 to each trial arm. Autistic adults are eligible if they meet the following criteria: (1) a clinically confirmed autism diagnosis and (2) aged 18 or over. Autistic adults are not eligible to take part if they meet one or more of the following criteria: (1) have had an NHS learning disability annual health check in the last 12 months or are anticipated to attend one in the next 3 months; (2) are unable to consent for themselves and do not have a relative or supporter who can consent for them, in keeping with England’s Mental Capacity Act; (3) people in the final stages of a terminal illness; (4) their GP considers it inappropriate to invite them.

### Participant identification and recruitment process

Participating practices will identify autistic adults to send a study information pack explaining the study and inviting participation. For those people unable to consent for themselves, the study information pack will be sent to a relative or carer (referred to as a ‘consultee’ in the Mental Capacity Act), asking them to advise whether the person should take part. The autistic adult or their consultee will then be asked to complete the measures from the perspective of the autistic adult. Easy read and short versions of all information sheets are available to possible participants. Interested autistic adults will complete an expression of interest form and send this to the research team. A member of the research team, RDN staff, or primary care staff will arrange a meeting with the prospective participant to discuss the trial in more detail and take informed consent using face to face, video, or telephone means, in line with the participant’s preference. See Appendix 1 for copies of the consent forms. After informed consent, the research team, RDN staff, or primary care staff will collect baseline data on participants. See Fig. 1 for the flow chart of trial procedure.

**Fig. 1 Fig1:**
[figure not shown]
Health checks for autistic adults trial procedure

### Randomisation

Practices will be randomised to the intervention (health check) arm or the control (usual care) arm prior to participant recruitment via computer-generated sequence blocks [2, 4, 23]. Randomisation will be stratified by practice list size (small < 10,000 and large ≥ 10,000). A member of the research team independent of trial data collection will oversee this process and inform the practices of the randomisation outcome. The research team will make autistic participants aware as to whether they are in the health check or usual care arm in the study information pack. Due to the design of this trial, it is not possible for practices or participants to remain blinded to group.

### Health check for autistic adults intervention

Primary care staff in the health check arm will undertake training on autism and health check delivery provided by the research team. Training will comprise two mandatory modules (modules 1 and 2) and one optional module (module 3). Module 1 is an autism awareness e-learning programme for primary care staff that takes approximately 30 min to complete [24]; module 2 is a 1-h online session that builds on module 1 knowledge and outlines the core components of the health check, its delivery, and barriers to engagement. Module 3 comprises a number of continuing professional development sessions aiming to build enhanced knowledge and skills related to the delivery of healthcare to autistic people.

The Health Check for Autistic Adults is a biopsychosocial developmental health check designed to improve access and engagement with healthcare services for autistic adults, enable the identification of physical health, mental health, and social needs in autistic adults, and provide an opportunity for health promotion, health monitoring, and signposting autistic adults to services for support.

The Health Check for Autistic Adults comprises Primary Care staff training (as described above), a Health Check Pre-Appointment Questionnaire (Health Check PAQ) completed by the autistic person (or their supporter), and a health check appointment with a health professional.

Health Check PAQ: The practice will send autistic participants the Health Check PAQ (paper or online version as preferred by the participant) to complete and return to them before their health check appointment. This questionnaire comprises three parts: (1) questions about the autistic participant and their communication and sensory needs; (2) questions about what reasonable adjustments the autistic participant would like to help them engage with and attend the health check appointment; (3) questions about the autistic participant’s general health and wellbeing, including physical and mental health symptoms/conditions known or suspected to be more prevalent in autistic people and conditions that result in high rates of morbidity, or mortality. The online version of the questionnaire will automatically produce a summary report containing key information which a member of the primary care staff will upload to the autistic participant’s health record. Primary care staff will create and upload to the participant’s health record a summary report for autistic participants completing a paper version using the information provided.

Prior to the health check appointment, primary care staff will read the relevant parts of the completed Health Check PAQ Summary Report and will aim to implement reasonable adjustments as requested by the participant. Where practices are unable to put all the requested adjustments in place, primary care staff will contact the participant to discuss what adjustments they can offer, unless the participant indicated that they would not like to be contacted on the Health Check PAQ.

The practice will invite autistic participants to attend a health check appointment after their Health Check PAQ is received. Autistic participants will receive a leaflet containing details about the health check appointment. An appropriate health professional will complete the Health Check appointment, taking account of the information in the Health Check PAQ Summary Report. The Health Check appointment covers health promotion, health screening, vaccinations, physical health, mental health, daily functioning, relationships and sexual health, a brief medication review, and a physical examination. The health check appointment takes around 45 min to complete. Practices will offer flexibility around how the health check appointment is conducted (i.e. face-to-face, via video, via telephone or home visit) in line with the autistic participant’s preference and needs. The health professional will always undertake the physical examination in a face-to-face appointment. The health professional will communicate a Health Action Plan to the autistic participant at the appointment (with a written copy offered) based on the discussions, including highlighting the needs identified. They will also arrange any tests, interventions, or onward referrals as part of NHS care based on the Health Action Plan.

### Usual care

Participants in the usual care arm will receive primary healthcare services as usual. They may receive other health checks routinely delivered as part of usual care.

### Measures

See Fig. 2 for the time points at which data are collected.

**Fig. 2 Fig2:**
[figure not shown]
Intervention and data collection time points

#### Baseline characterisation

Following informed consent, participants will complete baseline measures (on paper or online via Qualtrics software [25]). These comprise a set of self-report measures to enable characterisation of the individual’s autism profile, general ability, and demographics. Participants can choose to complete the measures independently or with support from a carer or supporter or the person taking consent (researcher, RDN staff, or primary care staff). The following self-report measures will be collected:Demographics: we designed a bespoke demographic questionnaire for the study with versions for autistic adults, carers and supporters, health professionals, and administrate staff. The autistic adult’s version includes questions about personal characteristics, their living situation, employment and education, learning ability, support needs, and health conditions. For other participants, demographic information about personal characteristics is collectedSocial Responsiveness Scale – Second Edition (SRS-2) [26] is a 65-item standardised self-report questionnaire used extensively to rate the social communication features of autistic adults and children. Reported estimates of internal consistency between 0.94 and 0.96 and predictive validity of the adult form found a specificity level of 0.60 and sensitivity of 0.86 [27]Waisman Activities of Daily Living Scale (W-ADL) [28] is a measure of independence validated in people with a broad range of developmental disability diagnoses. Analysis indicates that it is reliable over time (*κ* = 0.92–0.93), with high levels of internal consistency across disability groups (Cronbach’s *α* = 0.88–0.94) and criterion validity when compared to the Vineland Screener Adaptive Behavior Composite Score (*r* = 0.78)

#### Outcome measures

The primary outcome for the trial will be the incidence of new health needs or conditions detected and met at 9 months. The primary analysis will report the mean number of identified needs that are met for each group. A number of secondary outcomes will also be evaluated including the following: the extent of health monitoring and health promotion needs met at 9 months, the incidence of social needs identified at 9 months, change in participant or carer general health, changes in quality of life, and changes in primary and secondary health and social care resource usage and costs. The primary economic outcome will be the incremental cost per QALY gained at 9 months.

Effectiveness measures:Bespoke Health Records Data Collection Form: we will collect health and social data routinely recorded by practices alongside information about previous health checks and health screening. This was informed by data collection from Cooper et al. [12] and includes the following: short and medium term health outcomes including number and type of new health needs/new conditions/new manifestation of an existing or previously diagnosed condition identified, any referrals to secondary care and/or general hospitals and results, screening or treatments undertaken (including management of Quality & Outcomes Framework qualifying long term conditions and review of medications or other treatment plans), and whether these health needs/conditions were resolvedPrimary Care Outcomes Questionnaire (P-COQ [29]) is a standardised 24-item questionnaire to measure outcomes in primary care. Analysis has identified 4 domains (health and wellbeing, health knowledge and self-care, confidence in health provision, and confidence in health plan) with high levels of internal consistency across each domain (Cronbach’s *α* = 0.77–0.95) and correlate with comparator Patient-Reported Outcome Measures (PROMs)Bespoke Lifestyle Outcomes Questionnaire gathers information about lifestyle choices and health related behaviours

Acceptability and feasibility measures:Bespoke Health Check Evaluation Questionnaire gathers information about the experience of completing/receiving the Health Check PAQ and attending/delivering the health check appointment. This questionnaire will only be completed by those in the health check arm immediately after the health check. There are parallel versions for autistic adults, carers and supporters, and health professionalsAppointment acceptance and attendance rates: we will collect data on the acceptance of health check appointments in the health check arm. We will use a brief questionnaire to ask participants who did not attend an offered health check appointment why they did not attend

Digital tool measures:

Information about the digital version of the Health Check PAQ, e.g. time taken to complete and whether completed in one visit: We will gather data using a Health Check Evaluation Questionnaire and semi-structured interviews post-health check

Health economic measures:EQ-5D-5L [30] [31] is a standardised measure of health-related quality of life allowing for the calculation of QALYs, used by NICE routinely to measure intervention effectiveness [32]. There is evidence that the measure demonstrates convergent validity with all items of the World Health Organisation Five Wellbeing Index (WHO-5 [33])Short-Form Health Survey version 2 (SF-36v2) [34]) is a standardised measure of health-related quality of life. The SF-36v2 assesses eight health concepts: limitations in physical activities because of health problems, limitations in social activities because of physical or emotional problems, limitations in usual role activities because of physical health problems, bodily pain, general mental health (psychological distress and wellbeing), limitations in usual role activities because of emotional problems, vitality (energy and fatigue), and general health perceptions. The SF-36v2 has high precision and has been extensively validated as a tool to measure health-related quality of lifeBespoke Health Resource Usage Questionnaire: to capture data on primary and secondary healthcare resource usage, use of social services and prescribed medicationBespoke Time and travel costs questionnaire: to capture time and travel costs related to contacts with healthcare providers

A researcher, RDN staff, or primary care staff will collect baseline questionnaires. Follow-up measures will be collected by a researcher or RDN staff. We will allocate all participants a unique number that will identify them on all assessment forms throughout the trial. Questionnaires will be completed on paper or online (via Qualtrics software [25]) in line with participants’ preferences. To promote retention, we will update participants regularly on study progress via quarterly newsletters and participants will receive a £20 voucher after the 3-month follow-up and a £30 voucher after the 9-month follow-up. A researcher will input all paper data into a database, and this will be stored separately to identifying data. Data entry and validation will be a continuous process, with a proportion of double data entry of questionnaire data, so that we will identify and address problems immediately. We will carry out range checks of data values and manual checks of source data will be undertaken where required. Those completing online questionnaires using Qualtrics software will be sent a personalised link, linked to their unique ID number. A researcher will download online questionnaires onto secure servers and merge with the data from paper version for analysis. Supported by primary care and/or RDN staff, a non-blinded researcher will collect, anonymise, and securely store data collected from health records. This anonymised information will then be rated by members of the study team who are blind to trial arm allocation and who have not had contact with participants. We will manage missing questionnaire data at item level in accordance with the manual for each questionnaire. We will treat all study data in accordance with the latest directive on Good Clinical Practice (2005/28/EC). We will invite a sample of participants (autistic adults, carers and supporters, and primary care staff) to take part in an interview. A researcher will conduct and record semi-structured interviews face-to-face, via video, or telephone, in line with participants’ preferences. An external transcription agency will transcribe all interviews and a researcher will anonymise them.

### Internal pilot

As there had not been a feasibility and acceptability study before, we conducted a 6-month internal pilot in April to October 2023 to measure the rate of the following: recruitment to the health check and usual care arms, practice’s health check delivery, completion of measures, and retention. We compared the rates to pre-specified progression criteria: recruitment of ≥ 20 autistic people per trial arm = continue recruitment, recruitment ≥ 15 autistic people per trial arm = recruit additional practices and review after 3 months, recruitment of ≤ 10 autistic people = discuss options with funders. We also undertook a safety analysis once 20 health checks had been conducted (between March and July 2024). This focused on identifying any possible harms or adverse effects of undertaking the health check. The harms analysis will consider the frequency of potential harms recorded in the health records and those reported by autistic people, carers and supporters, and health professionals between the trial arms: distress or anxiety, depression or low mood, increased patient consultations, and other harms.

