### Adverse event recording

Serious adverse events are not anticipated in the study; therefore, any event will be recorded as an unexpected adverse event. We will record the following events: a significant (as reported by treating health professional) increase in anxiety symptoms, a significant (as reported by treating health professional) increase in low mood or depressive symptoms, suicidal ideation, physical or emotional harm resulting from additional investigations or healthcare services received, unnecessary physical investigations, any safeguarding concerns, or any other significant event. The chief investigators will immediately review serious events in accordance with the trial protocol and respond in accordance with relevant NHS protocols. We will report all serious events to the sponsoring NHS Trust and the reviewing REC as per the standard operating procedure of the sponsoring NHS Trust.

Newcastle University and Cumbria, Northumberland, Tyne, and Wear Foundation Trust have indemnified the trial.

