Participants who withdraw consent for the collection of routinely available data prior to month 9 will not be included in the primary outcome analysis. We do not anticipate there being missing data for the primary outcome as it is based on routinely collected data. Secondary analyses will be complete-case analyses. For outcomes that are significant, if there is substantial differential dropout between treatment groups, we will apply multiple imputation with at least 20 imputed datasets and undertake sensitivity analyses to explore the robustness of results to the missing not at random assumption. We will record and tabulate the number of serious adverse events per group.

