### Qualitative study of acceptability and feasibility of the health check

#### Participant identification and recruitment process

A sub-set of autistic adults, carers and supporters, and primary care staff (health professional and administrative staff) in the health check arm will be invited to take part in the qualitative study. Autistic adults, carers and supporters, and primary care staff will consent to take part in the qualitative study as part of the main trial consent process described above. Following health checks, the research team will send an information sheet and consent form to primary care staff involved in delivering the health check via email.

We will conduct interviews with up to 20 purposively sampled autistic adults, up to 20 carers and supporters, and up to 30 primary care staff from the health check arm. We will purposively sample autistic adults based on practice, age, gender, and responses from their health check evaluation questionnaire. We will also aim to purposively sample primary care staff based on role and the practice (rural vs urban, large vs small practices). Once selected, the participant will be invited to take part in the interview via email or letter (in line with participant’s preference) and will receive a copy of the information sheet to read again to remind them of the qualitative activities and how their interview data will be managed. The interviews will be conducted face to face or via video or telephone, in line with participants’ preferences, and will be recorded and transcribed verbatim for qualitative analysis.

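### Reported harms are to be compared between arms, but solicited reporting is described only in the health check arm

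*Protocol article*

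**What the plan says.** The Internal pilot section sets out the harms analysis. It names two kinds of source and a between-arm contrast: "The harms analysis will consider the frequency of potential harms recorded in the health records", together with "those reported by autistic people, carers and supporters, and health professionals between the trial arms". The harms listed are distress or anxiety, depression or low mood, more consultations, and other harms.

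Two instruments are described that reach participants, carers or supporters, and health professionals alike:

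- The Health Check Evaluation Questionnaire (Outcome measures, acceptability and feasibility measures) has a version for each group. Its use is restricted: "This questionnaire will only be completed by those in the health check arm immediately after the health check".
- The interviews (Qualitative study, Participant identification and recruitment process) draw on a subset of the same groups "in the health check arm will be invited to take part in the qualitative study". The ceilings are 20 autistic adults, 20 carers and supporters, and "up to 30 primary care staff from the health check arm", so up to 20 + 20 + 30 = 70 interviews, all in one arm.

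Other routes are not confined to one arm. The Adverse event recording section opens with "We will record the following events: a significant (as reported by treating health professional) increase in anxiety symptoms" and names no arm. The statistical analysis section adds: "We will record and tabulate the number of serious adverse events per group". Both arms complete follow-up measures (Study design). The Randomisation section states that practices and participants cannot be blinded.

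**The concern.** A comparison of harm frequencies is fair only if harms have the same chance of being noticed and counted in each arm. Here a health check participant, their carer and their clinician can each be asked about the experience straight after the appointment, and some again at interview. No form is described that asks the corresponding people in usual care about harms. Reporters who know the allocation may also attribute distress to a new appointment more readily than to ordinary care.

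The listed harm of more consultations raises a related problem. The appointment is itself a consultation of about 45 minutes. If it is counted, attending participants acquire one by design.

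Two misreadings are at stake: a safe health check could appear harmful, or a real harm could be dismissed as an artefact of closer questioning. The primary outcome is not affected.

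**Working it through.** The article states no harm rate, capture rate, test or threshold for harms, so there is no figure to reproduce. The check has two steps.

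**Step 1: sources by arm**

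| Source | Health check arm | Usual care arm | Where described |
|---|---|---|---|
| Health records | Yes | Yes | Outcome measures; Internal pilot |
| Adverse event recording | Yes | Not restricted by arm | Adverse event recording |
| Follow-up questionnaires | Yes | Yes | Study design; Outcome measures; Economic evaluation |
| Evaluation questionnaire | Yes | No | Outcome measures |
| Interviews | Yes | No | Qualitative study |

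The last two rows are the ones built around all three reporter groups. The follow-up questionnaires reach participants in both arms, but none is described as a harms form.

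**Step 2: what unequal capture would do**

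Let *p* be the true harm risk, equal in both arms. Let *s* be the share of harms found by sources common to both arms. Let *e* be the share of the remaining harms found, and counted, through the one-arm sources.

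- Observed risk, usual care: *p* × *s*
- Observed risk, health check: *p* × (*s* + (1 − *s*) × *e*)
- Apparent risk ratio: 1 + *e* × (1 − *s*)/*s*, which does not depend on *p*

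Example with *p* = 0.20, *s* = 0.5, *e* = 0.5: usual care 0.20 × 0.5 = 10%; health check 0.20 × (0.5 + 0.5 × 0.5) = 15%; ratio 1.50.

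The values of *p*, *s* and *e* are assumptions. The article gives about 100 participants per arm. The last column is the chance of a significant excess in the health check arm, using Fisher's exact test at two-sided 0.05 (also assumed) and ignoring clustering. The nominal limit in that direction is 2.5%.

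| *s* | *e* | Usual care | Health check | Ratio | Chance of significant excess |
|---|---|---|---|---|---|
| 0.5 | 0 | 10.0% | 10.0% | 1.00 | 1.4% |
| 0.5 | 0.25 | 10.0% | 12.5% | 1.25 | 5.3% |
| 0.5 | 0.5 | 10.0% | 15.0% | 1.50 | 13.8% |
| 0.5 | 0.8 | 10.0% | 18.0% | 1.80 | 30.7% |
| 0.3 | 0.5 | 6.0% | 13.0% | 2.17 | 30.8% |
| 0.3 | 0.8 | 6.0% | 17.2% | 2.87 | 64.0% |

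The table uses *p* = 0.20. Letting *p* run from 0.10 to 0.40 leaves the ratios unchanged and moves the chance, for *e* above 0, between 3% and 96%.

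The safety analysis was triggered by 20 health checks. With 20 per arm (the usual care number is assumed), the same grid gives 0.2% to 28%. At that size the main risk is misreading raw counts, not a significant test.

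The first row shows the effect of the remedy: with equal capture the expected ratio is 1.00.

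**The case against.** The strongest case against the point runs as follows.

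- **Pooling is not stated.** A reader might infer that all sources are added into one count. The Internal pilot section only lists sources whose frequencies will be considered. This objection stands. The point survives it, because a between-arm comparison of carer- or professional-reported harms is uneven even when each source is tabulated alone.
- **Usual care is not without a source.** A reader might infer that no harm reports can come from usual care. The documents do not support that. Adverse event recording is not limited to one arm, serious events are tabulated per group, and both arms complete follow-up measures. Anxiety and low mood qualify "as reported by treating health professional", and usual-care participants have treating professionals too. It would therefore be wrong to move all such reports to a one-arm listing, since that would discard usual-care events.
- **The link is inferred.** Nowhere does the article say that the evaluation questionnaire or interviews feed the harms analysis. They are to be summarised descriptively and analysed thematically. This is true, but the article names no other instrument through which all three groups would be asked, and it does commit to comparing their reports.
- **Detail belongs in the analysis plan.** Table layout does. Which sources support a stated between-arm contrast is a matter of validity, and the article has already worded that contrast.
- **Broad capture suits a search for possible harms.** It does, and the separate listing keeps it. The difficulty lies only in comparing the arms on it.
- **The article does not say the appointment will count as an extra consultation.** Correct. Excluding it is a clarification.

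Blinded rating of anonymised record data protects the rating step. It does not equalise what was recorded or reported.

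**Conclusion.** The point holds in limited form. The article plans a between-arm comparison of reported harms, while the only instruments described that could solicit reports from participants, carers and professionals alike are used in the health check arm. Reporters are unblinded. If those reports are counted, equal true harm could appear as excess harm in the health check arm.

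The direction follows from the design; the size is unknown. The ratios of 1.25 to 2.87 depend entirely on assumed capture rates (common sources finding 30% to 50% of harms, one-arm sources finding 25% to 80% of the rest). A reader might take them as an estimate of the bias in this trial, but the documents contain nothing that would support that. They show only that moderate differences in capture are enough to mislead. The change is cheap and worth making.

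**What to change.** State that the between-arm harms comparison uses only sources collected the same way in both arms:

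- Record extraction over a window of equal length, with its start stated for each arm. Follow-up is counted from the health check in one arm and from completion of baseline measures in the other.
- The trial-wide adverse event log, including treating-professional reports from both arms.
- The SF-36v2 and EQ-5D-5L at 3, 6 and 9 months, and the resource-use questionnaire at its scheduled follow-ups. The SF-36v2 covers psychological distress, and the resource-use form covers consultations.

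List harms that surface only through the evaluation questionnaire or interviews separately, labelled as health-check-arm data with no comparator. Leave the health check appointment itself out of the count of increased consultations.

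Add a caveat: the appointment covers mental health and may itself prompt recording or reporting of anxiety or low mood. Record-based and professional-reported harms are therefore not fully free of ascertainment bias, and this remedy does not remove it.

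The cost is a few sentences and a source column in the harms table, with no new procedure. The downside is fewer events in the comparative table, and so less precision.
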